### Statistical analysis

Patient’s baseline characteristics will be described for the study cohorts separately, using mean and standard deviation for continuous variables, or median and interquartile range in case of non-normality, and absolute and relative frequencies for categorical variables. Skewed variables will be transformed by the logarithm before the analysis. Data availability and the fraction of missingness will be assessed and reported for each variable. As the fraction of missing data is expected to be low, a complete case analysis will be carried out. Data screening through the computation of sample characteristics and visual inspections to identify the presence of missing values, skewed variable distributions, and outliers, as well as reporting of conducted screening activities will adhere to the conceptual framework for initial data analysis by Huebner et al. [25]. All analysis will be performed with the software R version 4.0.2.

### Prediction model development

People adhering to the inclusion and exclusion criteria from either the PROVALID or GCKD study will be considered for model building. Mixed-effects modeling accounts for the dependencies between repeated measurements per person over time and the similarity among people belonging to the same study cohort, hence they are commonly employed to analyze longitudinal and clustered data. Here, we will consider hierarchically nested random effects for the country and people within a country, such that the heterogeneity of eGFR trajectories between the five countries within the development cohort can be modeled appropriately [26]. More specifically, we will use random effects for the intercept and the slope of the repeated eGFR measurements over time and an additional random intercept for the country. We will include the baseline eGFR value in the outcome vector to provide more stable estimates of variability. When applying the model, any available eGFR measurements of an individual for whom eGFR trajectory predictions should be obtained can be used to improve predictions. A similar approach has been conducted by Selles et al. [27] to develop a prediction model not only able to deal with multiple measurements per subject but also able to allow these repeated clinical measurements to contribute to the prediction of an unseen individual. The set of clinical variables outlined in Table 2 will constitute the fixed effects. Automated variable selection will not be conducted as the set of predictors was chosen by background knowledge. Furthermore, due to the large sample size available for estimation overfitting is expected to be minimal, such that further regularization of the predictor effects will be omitted. Clinically relevant pairwise interactions of the independent variables with time will be investigated and added if their inclusion improves the prediction accuracy of the model as determined by the Akaike information criterion (AIC). Any model misspecification, e.g., regarding functional forms of the variables in the model, will be assessed using a plot of the marginal residuals versus the individual variables. Variables with non-linear relationships with the outcome as exhibited by these residual plots will then be modeled using restricted cubic splines to improve the model fit [28]. In addition, the relevance of the inclusion of such non-linear terms for improving the model fit will be evaluated in terms of the AIC.

More formally, the model for the continuous eGFR values *Y*_*it*_ at time point *t* (*t* = 0, …, *T*) for subject *i* (*i* = 1, …, *n*) is defined by
1$$ {\mathrm{Y}}_{\mathrm{i}\mathrm{t}}={\upbeta}_0+{\mathrm{a}}_{\mathrm{i}}+{\upbeta}_1X+{\upbeta}_2\mathrm{t}+{\upbeta}_3\mathrm{tX}+{\mathrm{b}}_{0\mathrm{i}}+{\mathrm{b}}_{1\mathrm{i}}\mathrm{t}+{\upepsilon}_{\mathrm{i}\mathrm{t}}, $$

with normally distributed residuals $$ {\epsilon}_{it}\sim N\left(0,{\sigma}_{\epsilon}^2\right) $$ with mean 0 and variance $$ {\sigma}_{\epsilon}^2 $$, random country-specific intercepts assumed to be *a*_*i*_~*N*(0, *τ*^2^), the random coefficients (*b*_0*i*_, *b*_1*i*_)~*MN*(0, *G*) (where MN denotes the bivariate normal distribution with an unspecified covariance matrix G, defined by the diagonal elements $$ {\upsigma}_0^2 $$ and $$ {\upsigma}_1^2 $$ and the off-diagonal σ_01_) and the vector of regression coefficients for the clinical independent variables *β* = (*β*_0_, *β*_1_, *β*_2_, *β*_3_). It should be noted that for simplicity of description, we here consider a single clinical predictor variable *X*, where *β*_1_ and *β*_3_ represent the regression coefficients corresponding to the clinical predictor variable and its interaction with time. Without loss of generality, more clinical predictors can be added, each with two regression coefficients for the baseline effects of the predictor and the corresponding interaction with time. When considering restricted cubic splines for a variable, this variable will be represented by several corresponding basis functions in (1).

Model (1) allows to prognosticate baseline and follow-up values of eGFR for a new person *j* given the value of the clinical predictor *X*, assuming that for that new person the random intercept and slope are equal to their expected values of 0. Further, we will assume the expected random country effect of *a*_*j*_ = 0 for the prediction of eGFR in a new individual. In order to incorporate a baseline eGFR measurement *y*_*j*0_ into the prediction, a best linear unbiased predictor (BLUP) of the individual’s random effects can be obtained through the posterior distribution of the random effects. The random intercept for that new subject *j* is then estimated by
2$$ {\hat{\mathrm{b}}}_{0\mathrm{j}}=\frac{\upsigma_0^2\left({\mathrm{y}}_{\mathrm{j}0}-{\hat{\mathrm{y}}}_{\mathrm{j}0}\right)}{\upsigma_0^2+{\upsigma}_{\upvarepsilon}^2}, $$

where $$ {\hat{\mathrm{y}}}_{\mathrm{j}0} $$ denotes the estimated baseline value from the fixed effects, $$ {\sigma}_{\epsilon}^2 $$ denotes the variance of the random error and $$ {\sigma}_0^2 $$ the variance of the random intercept in the covariance matrix of the random coefficients *G*. The estimated random slope $$ {\hat{b}}_{1j} $$ for the new individual can be obtained by
3$$ {\hat{\mathrm{b}}}_{1\mathrm{j}}=\frac{\upsigma_{01}{\hat{\mathrm{b}}}_{0\mathrm{j}}}{\upsigma_0^2} $$

In actual predictions, estimates are plugged in for $$ {\sigma}_o^2 $$, σ_01_, and $$ {\upsigma}_{\upvarepsilon}^2 $$. The preliminary prediction $$ {\hat{y}}_{jt} $$ for the new subject *j* at time *t* can then be updated by
4$$ {\overset{\sim }{\mathrm{y}}}_{\mathrm{jt}}={\hat{\mathrm{y}}}_{\mathrm{jt}}+{\hat{\mathrm{b}}}_{0\mathrm{j}}+\mathrm{t}{\hat{\mathrm{b}}}_{1\mathrm{j}} $$

The predicted eGFR slope for a new individual, combining fixed and random effects, is finally given by $$ d\tilde{y}_{j}:= d{\overset{\sim }{\mathrm{y}}}_{\mathrm{j}\mathrm{t}}/ dt={\hat{\upbeta}}_2+{\hat{\upbeta}}_3{\mathrm{X}}_{\mathrm{j}}+{\hat{\mathrm{b}}}_{1\mathrm{j}} $$ with $$ {\overset{\sim }{V}}_j $$ expressing the variance of the predicted eGFR slope of individual *j*.

Given a correct model specification, the probability of progression can then be obtained by a normal approximation:
5$$ \Pr \left(\mathrm{Z}={\mathrm{z}}_{\mathrm{j}}\right)=1-\Phi \left(\frac{{\mathrm{C}}_{\mathrm{p}}-d{\overset{\sim }{\mathrm{y}}}_{\mathrm{j}}}{\sqrt{{\overset{\sim }{V}}_j}}\right) $$

where *z*_*j*_, *j* ∈ {1, 2} denotes the membership of belonging to one of the two progression groups: rapid and stable progression, and Φ(x) the standard normal distribution function at *x*. *C*_*p*_ is the corresponding subject-specific cutpoint for defining progression of kidney decline, which will be set to −3mL/min/1.73m^2^/year at default or can be specified by the intended user in the web application (see Section "Web implementation") [14–16]. Now, one can compute the expected probability of belonging to either of the eGFR progression groups given a patient’s baseline characteristics and the baseline eGFR.

For all statistical analyses, the freely available software R will be used. Mainly, the packages *nlme* and *JMbayes* will be considered for the implementation of the linear mixed model and the subject-specific prediction informed by the baseline eGFR measurement. The function *lme()* from the package *nlme* will be used to fit the linear mixed model and the function *IndvPred_lme()* from the package *JMbayes* to obtain the updated predictions and 95% prediction intervals for a new subject.

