Nevertheless, several prediction models for the progression of renal function decline have previously been developed in various populations. It is of note that the models which were developed in studies from the last decade may no longer be applicable nowadays, because the new treatment classes of SGLT2-blocker and mineralocorticoid receptor antagonists have dramatically changed the course of CKD progression [6–8]. In addition, existing predictive models have mainly considered hard renal endpoints such as incidence or end-stage renal failure [9, 10]. Studies focused on renal function have mainly considered simplifications of the longitudinal eGFR trajectory by dichotomization of the expected eGFR slope. For instance, Subasi et al. [11] conducted a pilot study based on a randomized double-blinded treatment trial, the African American Study of Kidney Disease and Hypertension (AASK), in order to predict the rate of kidney function decline. The least-squares slopes of GFR decline from the 6-month time point until censoring were used to define rapid (i.e., an absolute slope < 3mL/min/1.73m^2^/year) and slow (i.e., absolute slope in between 1 and 3mL/min/1.73m^2^/year) progressors for this study. Similarly, Vigil et al. [12] aimed towards the identification of predictors of a rapid decline of renal function defined as an annual eGFR loss > 4 mL/min/1.73m^2^. However, covariates considered for selection in this analysis were chosen on the basis of their significance in univariable analysis (or by their clinical or biological relevance). Despite its popular use for data reduction, univariable prefiltering has been shown to lead to suboptimal or biased selection results [13]. Pena et al. [14] showed that a panel of novel biomarkers improves the prediction of renal function decline in people with DM2. In contrast to the other mentioned studies, renal function decline was not dichotomized. The eGFR slope was estimated using linear regression and then constituted the outcome of interest in its continuous form. People with an observed eGFR decline larger than −3mL/min/1.73m^2^ were considered stable, all others were considered to be rapid progressors in terms of kidney function decline. Then, a person’s risk was assessed by dichotomizing the observed decline in these two groups and comparing it with the predicted probabilities of eGFR decline. The threshold of −3mL/min/1.73m^2^ was selected based on literature, which however included older studies without the current state-of-the-art therapy of diabetic kidney disease, where a GFR loss of only 1mL/min//1.73m^2^/year is standard [14–17]. Furthermore, molecular data in regular clinical care is usually not easily available and no validated reference values exist for these markers.

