
In this study, we will apply state-of-the-art methodology to avoid deficiencies of previous attempts in prediction models for renal function decline. We will directly incorporate the repeated eGFR measurements per person as an outcome vector into a multivariable mixed-effects model accounting for the dependence of the repeated measurements of eGFR and the clustered data structure due to the use of two multicenter prospective study cohorts. We will also provide the methodology to condition a prediction on an available baseline value of eGFR, facilitating predictions regardless of whether a baseline eGFR is available or not. In contrast to the commonly applied approaches, the repeated values of eGFR across follow-up visits will not be used for slope estimation followed by categorization to infer groups of the severity of loss in kidney function (e.g., stable, mild, and rapid progression) prior to model development. The proposed approach will enable the identification of groups of patients with a high risk of rapid renal function decline by longitudinal prediction of subject-specific eGFR trajectories, thereby providing the probability of exceeding a prespecified cutpoint of eGFR decline per year. After the planned external validation, our model will be implemented as a web tool and can be clinically applied to identify people with DM2 at increased risk of rapid decline in kidney function, or as a supporting tool for clinicians in medical decision-making so that patients can be prompted to seek medical care before a significant deterioration in kidney function occurs.

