### Web implementation

The externally validated model will be implemented as an interactive prediction calculator, made available online as a web application to support clinical care and medical decision-making with regard to prevention and treatment of chronic kidney function decline in people with DM2. The interactive web application will be created with the help of the R development framework *shiny* to allow for individual input and the computation of patient-specific predictions given their baseline characteristics. The web application will offer two user interfaces to choose from:
A patient interface with a web layout consisting of limited input controls (i.e., text fields or checkboxes to enter age, sex, eGFR, and UACR)A clinician interface with a layout featuring input controls for all predictors (i.e., includes laboratory measurements, medication) within the validated prediction model

Both interfaces will be based on the same prediction model formula, with predictors that are excluded from the web layout in the patient interface being fixed as the average value for the continuous variables and the value with the highest relative frequency for the categorical variables. As a result, the use of the model should not only be made available to clinical staff but also to patients themselves.

The output of the web application will contain the following components:
The eGFR value estimated by the model in 1–5 years with 95% model-based prediction intervalsThe predicted eGFR decline per year with 95% model-based prediction intervalThe proportion of people with higher predicted eGFR lossThe relative risk, i.e., the probability for a rapid eGFR decline for the predicted interval divided by the probability of a rapid eGFR decline for a person with equal age, sex, and baseline eGFR, but most favorable values of all other clinical baseline variables (with rapid decline specified by the intended user)A visual representation of the results:The visual communication of the results to the user will illustrate the estimated eGFR decline in the context of the distribution of predicted eGFR declines in the development cohort. In addition, a figure will be generated that shows the predicted trajectory of eGFR over the next 5 years with a 95% prediction interval.

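### Eq. (5) is introduced as the probability of progression but prints the opposite tail, the probability of a stable course

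*Protocol article*

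**What the plan says.** All of the following is in the protocol article.

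- **Slope.** Prediction model development, after Eq. (4): "The predicted eGFR slope for a new individual, combining fixed and random effects, is finally given by" the time derivative of the updated prediction, β̂₂ + β̂₃X_j + b̂₁j. This is a signed quantity, negative when eGFR falls.
- **Cutpoint.** Same section: C_p is the value "which will be set to −3mL/min/1.73m^2^/year at default or can be specified by the intended user in the web application". It is on the same signed scale.
- **Probability.** Same section: "the probability of progression can then be obtained by a normal approximation". Eq. (5) follows as Pr(Z = z_j) = 1 − Φ((C_p − slope)/√V_j). The symbol z_j "denotes the membership of belonging to one of the two progression groups: rapid and stable progression". The text does not say which value of the index is rapid and which is stable. It adds that the probability of membership of either group can now be computed.
- **Variance.** V_j is introduced as "expressing the variance of the predicted eGFR slope of individual" j, with no formula.
- **Stated aim.** The Introduction promises predictions "thereby providing the probability of exceeding a prespecified cutpoint of eGFR decline per year".
- **Direction of the −3 threshold.** The Introduction describes an earlier biomarker study in which people whose eGFR change lay above −3 "were considered stable, all others were considered to be rapid progressors in terms of kidney function decline".
- **Later uses.** Model evaluation, performance, and external validation plots the mean estimated risk of fast progression by decile against the observed proportion. Web implementation defines a relative risk as "the probability for a rapid eGFR decline for the predicted interval divided by the probability of a rapid eGFR decline" for a person with the most favourable values of the remaining predictors.

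**The concern.** Every use the article makes of this probability needs the chance of rapid decline: the aim in the Introduction, the decile calibration plot, the rapid/stable option in the web application, and the relative risk. Eq. (5) is the only formula given for it. With a signed slope and a negative cutpoint, the printed formula gives the other group's probability.

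An implementer who followed the equation and its lead-in literally would give people with steep predicted decline a low risk and people with a flat trajectory a high one. The web application is meant for patients as well as clinicians, so the printed formula should be right before anyone codes from it.

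**Working it through.** **Inputs.** C_p = −3 and the signed slope come from Prediction model development. The article gives no value for V_j, so SD = √V_j is assumed over a range of 0.5 to 3 mL/min/1.73m²/year. The article also gives no numerical result for Eq. (5), so there is no figure of its own to reproduce.

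**Step 1: which tail.** Treat the person's slope S as normal with mean s (the predicted slope) and standard deviation SD.

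- Rapid decline: P(S < C_p) = Φ((C_p − s)/SD).
- Stable course: P(S > C_p) = 1 − Φ((C_p − s)/SD).

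Eq. (5) as printed is the second line. Simulation with 400,000 normal draws per case agreed with P(S > C_p) to within 0.002.

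**Step 2: size at SD = 1, C_p = −3.**

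| Predicted slope | (C_p − s)/SD | Eq. (5) as printed | P(rapid) |
|---|---|---|---|
| −6 | 3 | 0.0013 | 0.9987 |
| −4 | 1 | 0.159 | 0.841 |
| −3 | 0 | 0.500 | 0.500 |
| −1 | −2 | 0.977 | 0.023 |
| 0 | −3 | 0.999 | 0.001 |

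**Step 3: dependence on the assumed SD, at slope −6.**

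| SD | (C_p − s)/SD | Eq. (5) as printed | P(rapid) |
|---|---|---|---|
| 0.5 | 6 | 0.000 | 1.000 |
| 1 | 3 | 0.001 | 0.999 |
| 2 | 1.5 | 0.067 | 0.933 |
| 3 | 1 | 0.159 | 0.841 |

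The size of the gap depends on SD, but the direction does not. The printed value is always 1 − P(rapid), so ranking people on it reverses the ranking on P(rapid) exactly, for any V_j.

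**Step 4: relative risk in Web implementation.** Assume an index slope of −5, a favourable-reference slope of −1, and the same SD for both.

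- SD 2, lower tail: Φ(1)/Φ(−1) = 0.8413/0.1587 = 5.3. As printed: 0.1587/0.8413 = 0.19.
- SD 1: 43.0 with the lower tail, 0.023 as printed.
- SD 3: 3.0 with the lower tail, 0.34 as printed.

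**Step 5: can another sign convention rescue the equation?** If slope and cutpoint were both positive losses, a loss of 6 against a cutpoint of +3 at SD 1 gives 1 − Φ(−3) = 0.9987, and the printed form would be right. The article rules this out by defining the slope as a derivative and setting C_p to −3. Mixing the conventions (positive loss, C_p = −3) gives nearly 1 for everyone: at SD 1 a loss of only 1 gives 1 − Φ(−4) = 0.99997.

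**Step 6: can one expression serve both groups?** The two probabilities sum to 1, so a single right-hand side can equal both only when each is 0.5.

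**The case against.** The strongest defence is that Pr(Z = z_j) is a generic label. Eq. (5) could then be the stable-group probability, with rapid decline as its complement. This reading is possible, but nothing in the text adopts it. Neither group is assigned to the expression, the index j already denotes the new individual, and the only verbal label is progression. On this reading too, the equation needs a group label.

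A reader might go further and infer that the tool will rank the fastest decliners as lowest risk. The documents do not support that as a fact. No code is shown, and the slip may be typographical. The intended direction is clear elsewhere in the article. The decile plot is planned for the internal-external validation and for DIACORE, and a swapped tail would show there as an inverted plot. Web implementation refers to the externally validated model, so that check comes before release. The link from Eq. (5) to the decile plot and the relative risk is itself a reasonable inference, because neither section cites the equation. However, the other performance measures (Kendall's tau-b, the eGFR calibration regression and adjusted R²) concern eGFR itself and would not reveal the error.

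A reader might also infer that V_j is the wrong variance, namely the spread of the predicted slopes between people and not the remaining uncertainty about one person's slope. The article proposes no such quantity. It gives no formula for V_j, works from the posterior distribution of the random effects, names a function that returns prediction intervals for a new subject, and promises a prediction interval for the annual decline. All of this fits a conditional prediction variance. The missing formula is a matter for clarification, not an error.

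**Conclusion.** Eq. (5) is wrong as written for the quantity its text names. The finding rests only on the signed slope and the cutpoint of −3, both fixed in the article, and it holds for any V_j. The sizes shown rest on assumed SDs of 0.5 to 3 and, for the relative risk, on assumed slopes of −5 and −1.

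The practical consequence is conditional: reversed ranking and an inverted relative risk follow if the equation is coded as printed and its output is reported as the risk of rapid decline. Eqs. (1) to (4), the predicted eGFR values and the predicted slopes are not affected. The equation should be corrected before the model is implemented or validated on risk deciles.

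**What to change.** Replace Eq. (5) with two labelled lines:

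- Pr(rapid) = Φ((C_p − slope)/√V_j)
- Pr(stable) = 1 − Pr(rapid)

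Use a group index other than j. State that Pr(rapid) is the quantity used in the risk-decile plot, the rapid/stable option and the relative risk. If a user may enter the cutpoint, state that it is entered as a signed slope.

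As a clarification only, add that V_j is the prediction variance of the individual's slope given the available eGFR values, including estimation error.

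The cost is one equation and two or three sentences, with no change to data, design or model fitting. Any code already written should be checked with one case: at C_p = −3, a predicted slope of −6 must return a probability of rapid decline above 0.5.

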### Model evaluation, performance, and external validation

An analysis of the conditional residuals will be conducted to check correct model specification, e.g., normality, linearity, and homoscedasticity of the error terms. Next, the importance of each independent variable will also be evaluated by the drop in the adjusted *R*^2^, i.e., the loss in estimated explained variation when the respective predictor is removed from the model.

The performance of the prediction model will be evaluated by an internal-external validation procedure to obtain a reliable assessment of its generalizability of prediction to unseen data [29]. The unit for the non-random data splitting will be the six countries within the PROVALID and GCKD studies (GCKD: Germany; PROVALID: Austria, Hungary, Netherlands, Poland, and Scotland) such that for each iteration, one regional group with its study participants are withheld from model training and then used for testing.

The prediction performance will further be assessed through:
Discrimination in terms of Kendall-tau-b concordance correlation coefficients at each time point, i.e., the concordance of the predicted eGFR values at time *t* obtained by Eq. (4) and the actual observed eGFR in each pair of patientsCalibration in terms of the slope of the calibration curve by
I.Regressing the predicted eGFR on the actual eGFR values at each time pointII.Plotting the estimated mean risk for fast progression per decile against the observed ratio of fast progression within each risk decileExplained variation in terms of adjusted *R*^2^, i.e., the proportion of explained variability in the outcome by the independent variables

The external validity of the model will be examined by applying the final prediction model to the DIACORE study cohort and evaluating the three performance measures outlined above.

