#### PROVALID - PROspective cohort study in patients with type 2 diabetes mellitus for VALIDation of biomarkers

The PROVALID study cohort consists of around 4000 people with DM2 of whom information on medical history, physical status, laboratory measurements, and medication have been prospectively collected. Patients who are being taken care of at the primary healthcare level in five European countries (Austria, Hungary, Netherlands, Poland, and Scotland) were recruited between 2011 and 2015 and followed for at least 5 years. Participants had to be aged 18–75 years and had an incident or prevalent DM2 defined as treatment with hypoglycaemic drugs or according to ADA guidelines at the time point of study entry. The presence of CKD at study entry was not an exclusion or inclusion criterion. For the full inclusion and exclusion criteria of patients, see Table 1. The aim of the study was to investigate regional differences in the course of diabetic nephropathy to determine the 5-year cumulative incidence of renal and cardiovascular outcomes and to identify predictive biomarkers for the eGFR trajectory in patients with DM2.

**Table 1 Tab1:** Overview of the inclusion and exclusion criteria of PROVALID, GCKD, and DIACORE

Study cohort	Study setting	
	Inclusion	Exclusion
PROVALID	▪ Aged 18–75 years ▪ Incident or prevalent DM2 with/without CKD	• Active malignancy requiring chemotherapy
GCKD	▪ Aged 18–74 years ▪ Caucasian ethnicity ▪ eGFR: 30–60 mL/min/1.73m^2^with or without urinary albumin excretion ▪ eGFR > 60 mL/min/1.73m^2^ - Albumin excretion of > 300mg/g creatinine - Proteinuria > 500mg/day	▪ Active malignancy in the 24 months prior to inclusion ▪ Renal or other transplantations ▪ NYHA IV heart failure
DIACORE	▪ Aged ≥ 18 years ▪ Caucasian ethnicity ▪ Prevalent DM2	▪ On chronic renal replacement therapy ▪ Active malignancy ▪ Pregnancy ▪ Further diseases and infections

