#### GCKD—German chronic kidney disease

The prospective cohort study GCKD consists of around 5000 people with CKD. Patients aged 18–74 years and suffering from CKD were included in case of an eGFR between 30 and 60 ml/min/1.73m^2^ with or without urinary albumin excretion (CKD KDIGO Stage 3) or a better preserved eGFR in the presence of urinary albumin excretion >300 or protein excretion >500mg/day, and were followed up to 10 years. For the full inclusion and exclusion criteria of patients, see Table 1. Out of the 5000 recruited individuals, 1800 had diabetes and therefore represent the relevant patient subset for the prediction model in this work. The follow-up visits were set up in bi-yearly intervals. The main objective of the GCKD study cohort was to identify and validate risk factors for CKD, end-stage renal disease (ESRD), and cardiovascular disease (CVD) events.

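### The planned eGFR performance measures all depend on the spread of eGFR, and no absolute error is named, so the Germany (GCKD) fold can look worse at equal prediction error

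*Protocol article*

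**What the plan says.** The section on model evaluation, performance and external validation withholds one country at a time: "The unit for the non-random data splitting will be the six countries within the PROVALID and GCKD studies". Germany is GCKD; the other five countries are PROVALID. The stated aim is "to obtain a reliable assessment of its generalizability of prediction to unseen data".

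Three kinds of measure are named:
- discrimination: "Discrimination in terms of Kendall-tau-b concordance correlation coefficients at each time point", comparing Eq. (4) predictions with observed eGFR;
- calibration: (I) a slope with predicted eGFR as the response and actual eGFR as the regressor, at each time point, and (II) a plot of predicted against observed fast progression by risk decile;
- explained variation: adjusted R².

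DIACORE is then assessed by "evaluating the three performance measures outlined above". No RMSE, mean absolute error or other error in eGFR units appears.

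The two development cohorts differ in entry. For PROVALID, "The presence of CKD at study entry was not an exclusion or inclusion criterion". GCKD patients were "included in case of an eGFR between 30 and 60 ml/min/1.73m^2^ with or without urinary albumin excretion", or with "a better preserved eGFR in the presence of urinary albumin excretion >300 or protein excretion >500mg/day". The target population adds a common floor of baseline eGFR above 30.

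**The concern.** Tau-b and R² describe how well predictions separate people relative to how much those people differ. A held-out group with a narrow range of eGFR scores lower than one with a wide range, even if each person is predicted with the same error. Germany is the only fold in the internal-external step that crosses from one study to the other, and it is also the fold selected on the outcome variable.

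The planned calibration slope does not separate the two effects. With predicted eGFR regressed on actual eGFR, a perfectly calibrated model does not give a slope of 1. It gives the ratio of predicted to observed variance, which again depends on spread.

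At stake is how a low figure for Germany would be read: as poor transport of the model, or as a consequence of who was enrolled. The planned numerical eGFR measures cannot distinguish these. The web tool will also show eGFR values for years 1 to 5, and no planned measure states the held-out error in the units that its users will see.

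**Working it through.** **Plan's own figures.** The article gives no performance figure by country. Its sample-size section supplies the scale: mean eGFR 78.4, SD 21.4, anticipated R² 0.3, 13 predictors. The minimum sample sizes stated there (271, 3048, 1569, 903) reproduce exactly.

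**Assumptions, not in the article.** Residual SD 7 (also 5 and 9), slope SD 1.5 per year, no intercept-slope covariance, prediction at year 4. R² is taken as the explained variation of the Eq. (4) predictions. The same true model holds in every fold, so transport loss is zero by construction.

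**Step 1: prediction error.**
- Fixed-effect variance: 0.3 × 21.4² = 137.4.
- Random-intercept variance: 0.7 × 21.4² − 7² = 320.6 − 49 = 271.6.
- Weight in Eq. (2): k = 271.6 / 320.6 = 0.847.
- Error variance at year 4: 271.6 × 49 / 320.6 + 4² × 1.5² + 49 = 41.5 + 36 + 49 = 126.5, so RMSE = 11.2.

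This does not depend on baseline eGFR, so it is the same in every fold.

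**Step 2: variance of the predictions.** Apart from a constant, Eq. (4) gives (1 − k) × fixed part + k × baseline eGFR. Given baseline eGFR, the fixed part has regression slope 0.3 and variance 0.3 × 0.7 × 21.4² = 96.2. Hence V = (0.847 + 0.153 × 0.3)² × Var(baseline) + 0.153² × 96.2 = 0.797 × Var(baseline) + 2.2.

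**Step 3: the measures.** For a calibrated prediction, R² = V / (V + 126.5). The planned slope, Cov(predicted, actual) / Var(actual), is the same quantity. The slope of observed on predicted is 1.
- Unselected above 30 (SD 20.6): V = 0.797 × 424.4 + 2.2 = 340.4; R² and planned slope = 340.4 / 466.9 = 0.73.
- Strict 30-60 (SD 7.5): V = 0.797 × 56.3 + 2.2 = 47.1; R² and planned slope = 47.1 / 173.6 = 0.27.

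**Step 4: simulation, 20,000 people per fold, same parameters.** Those above 60 in the GCKD-like folds are a random part of the same upper tail.

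| Fold | Share >60 | SD | tau-b | R² | Planned slope | Observed on predicted | RMSE |
|---|---|---|---|---|---|---|---|
| PROVALID-like, >30 | 81% | 20.58 | 0.66 | 0.73 | 0.73 | 1.00 | 11.25 |
| GCKD-like | 0% | 7.56 | 0.34 | 0.27 | 0.27 | 0.98 | 11.20 |
| GCKD-like | 10% | 13.75 | 0.44 | 0.54 | 0.55 | 0.99 | 11.27 |
| GCKD-like | 18% | 16.91 | 0.51 | 0.65 | 0.65 | 1.00 | 11.18 |
| GCKD-like | 31% | 19.96 | 0.59 | 0.72 | 0.72 | 1.01 | 11.25 |
| GCKD-like | 52% | 22.17 | 0.66 | 0.76 | 0.75 | 1.00 | 11.34 |

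The largest gap is 0.66 − 0.34 = 0.32 in tau-b and 0.73 − 0.27 = 0.46 in R². With residual SD 5 the corresponding pairs are 0.72 and 0.43 (tau-b), 0.82 and 0.39 (R²). With residual SD 9 they are 0.58 and 0.30, 0.63 and 0.20. The 52% fold shows no loss at any of the three.

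**Step 5: where above 60 the patients lie.** This used a simpler simulation with a calibrated prediction and error SD 10. The PROVALID-like fold has R² 0.81 and tau-b 0.72. With 40% above 60, R² is 0.64 and tau-b 0.59 if they lie just above 60, and 0.82 and 0.68 if they are spread like the general upper tail.

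**Adjustment.** With 13 predictors and about 1800 people the adjustment factor is 1799 / 1786 = 1.007, so using adjusted R² changes nothing here.

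**The case against.** Five points can be made against this.

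- **GCKD is not a hard 30-60 band.** A reader might infer that Germany will look much worse. The entry rules do not support this, because a higher eGFR is admitted with albuminuria or proteinuria and the share is not given. Step 4 shows the gap can vanish. A clear gap with many patients above 60 needs them to lie just above 60, or a GCKD source mean near 60, and the article states neither. This stands and limits the size.
- **Calibration is also planned.** This stands in part. The slope as written shares the defect. The decile plot is a different quantity; it concerns risk of fast progression, not the eGFR value, and was not tested here.
- **No misreading is planned.** The article sets no ranking of countries and no threshold, and baseline characteristics will be described by cohort, so the case-mix difference will be visible. This stands: a wrong conclusion on generalizability is a risk of interpretation, not a planned step. Seeing the difference in case mix still does not tell the reader how much of a low tau-b it explains.
- **DIACORE.** A reader might infer the same distortion there. Table 1 shows no eGFR entry band for DIACORE, and nothing in the article shows a narrower spread than PROVALID. DIACORE also gives separate evidence on transport to another study. This stands.
- **An article condenses the full plan.** An extra metric could sit elsewhere. But the article names its measures and applies the same three externally. The point is that this stated set is not enough for the stated purpose.

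**Conclusion.** The concern holds in a limited form. Tau-b, R² and the planned slope of predicted on actual eGFR all move with the spread of eGFR in the held-out group, and the article names no absolute error. Germany coincides with a cohort selected on eGFR, so a lower figure there cannot by itself be read as poorer transport.

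The size is uncertain: from no gap to about 0.3 in tau-b and about 0.45 in R² and planned slope, at equal RMSE of about 11.2 and an observed-on-predicted slope of about 1. The upper end needs almost all GCKD patients in 30-60. The range rests on the assumed residual SD, slope SD and normal shape around 78.4, and above all on the share and position of patients above 60. The documents do not support saying that Germany will look much worse or that generalizability will be misjudged. This is a worthwhile, cheap improvement to the evaluation and does not invalidate the model.

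**What to change.** For each held-out country and for DIACORE, at each follow-up time:
- add RMSE and mean absolute error of the Eq. (4) predictions in mL/min/1.73m²;
- add the calibration slope of observed on predicted eGFR, for which a value of 1 is the target whatever the spread;
- print the eGFR SD of the held-out group beside tau-b and R².

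State that transport is judged on the error and calibration measures, with tau-b and R² read in the light of each fold's case mix. Optionally, set each tau-b and R² beside the value expected if the fitted model were true, obtained by simulating outcomes from it at that fold's own covariates and baseline eGFR.

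The cost is a few extra table columns from predictions already produced. The optional benchmark adds a short simulation.
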